Our specific hypotheses include that: (1) early (<2 hours) USPIO-enhanced imaging will principally reflect vascular distribution and will correspond with other MRI-derived measures of tumor vascular density and perfusion; (2) delayed (24–48 hours) USPIO-enhanced imaging will principally reflect intracellular USPIO distribution within TAM, and will co-localize with but also extend beyond imaging (GBCA enhancement) and tissue markers of endothelial disruption; (3) that QSM-derived susceptibility estimates and T2*-based measures will provide optimal quantitative reliable measures of TAM density, iron abundance and cellular iron localization with imaged tumors; (4) susceptibility based measures of delayed USPIO uptake (e.g., QSM, R2* mapping) will be greater in growing VS, relative to non-growing tumors, and will reflect an increased abundance of TAM in these tumors; and (5) that regions of higher grade transformation within imaged glioma will show changes on delayed USPIO-enhanced acquisitions, in particular susceptibility-based measures such as QSM, and these regions will show greater TAM abundance on matched tissue sections compared to non-enhancing tumor regions.

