Scan 2 is performed within two hours of the ferumoxytol infusion, and incorporates the same T_1_W imaging, T_1_ relaxivity (R_1_) mapping, SWI, T_2_ and T_2_* mapping and QSM protocol used for the baseline scan. This short (<20 minutes) imaging protocol allows for the evaluation of ferumoxytol-related alterations in brain and tumor vasculature at this early timepoint. Visits 2 and 3 (scans 3 and 4) occur 24 and 48 hours, capturing the expected peak of USPIO uptake in TAMs post-infusion. During these subsequent visits, patients undergo the same brief MRI protocol as conducted at scan 2. This will enable the assessment of delayed (>24 hours) ferumoxytol-related imaging changes relative to baseline.

Since participants receive both GBCA and ferumoxytol, potential interactions between contrast-agent effects will be considered during image interpretation. Prior protocol optimization phantom experiments performed by our group, which demonstrated how GBCA is expected to predominantly influence T_1_-weighted and R_1_ measurements, whereas ferumoxytol is expected to exert stronger effects on T_2_, T_2_*/R_2_/R_2_*, SWI and QSM-derived susceptibility measures (unpublished). Accordingly, GBCA-enhanced imaging will primarily be used to define conventional enhancement and permeability-related tumor regions, while delayed ferumoxytol assessment will prioritize T_2_, T_2_*/R_2_/R_2_*/SWI and QSM-derived measures. The acquisition of R_1_, R_2_, R_2_*, T_2_*, T_2_, SWI and QSM data across pre-contrast, post-GBCA, early post-ferumoxytol and delayed post-ferumoxytol timepoints will also allow the *in vivo* signal effects of each contrast agent to be assessed across complementary quantitative imaging markers.

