Dual-injection dual-temporal-resolution DCE-MRI data will be analyzed using the LEGATOS method [34] to derive high-spatial-resolution maps of the following key microvascular parameters: volume transfer constant (*K*^*trans*^), plasma volume fraction (_*Vp*_) and extravascular extracellular volume fraction (_*Ve*_). SWI data acquired at each timepoint will be analyzed using the ‘Segregation and Extravascular Localization of Ferumoxytol Imaging’ (SELFI) formula, which aims to characterize USPIO nanoparticle intra/extravascular compartmentalization [27]. SWI magnitude images acquired at pre-contrast, early post-ferumoxytol, and delayed post-ferumoxytol time points will be co-registered to non-contrast-enhanced T_1_-weighted images. Voxel-wise logarithmic signal intensity ratios will be calculated between pre-contrast and ‘early’ SWI maps or delayed post-contrast images to estimate relative USPIO concentrations. Subtraction of delayed from early ratio maps will yield positive SELFI^+^ and negative SELFI^–^ values. SELFI^+^ values are thought to reflect extravascular USPIO uptake localized to phagocytic cells (TAMs), whereas SELFI^–^ values indicate persistent intravascular USPIO signal, consistent with regions of higher microvascular density [27]. SELFI values will be compared with maps of quantitative relaxometry values (T_2_*, T_2_) generated using existing pipelines and QSM-derived susceptibility maps. As the SELFI method is an investigational approach and not yet an established clinical biomarker, it may be influenced by image registration error, susceptibility artifact, baseline hemorrhage or calcification, residual intravascular USPIO, and nonlinear signal behavior on SWI magnitude images. SELFI maps will therefore be interpreted alongside QSM, T_2_*, SWI and tissue-based measures rather than as a stand-alone marker of cellular USPIO uptake.

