### Data collection, management, and analysis

2.8.

Multimodal imaging analysis will assess the relationships between USPIO uptake and tumor vascular, microstructural, and inflammatory characteristics. Spatial associations will be examined between ferumoxytol-sensitive imaging markers (T_2_, T_2_*, SWI and SELFI values, QSM derived susceptibility values), ASL and DCE-MRI–derived microvascular parameters (*K*^*trans*^, *Ve, Vp*, blood flow), and diffusion metrics (mean diffusivity and fractional anisotropy) using voxel-wise and region-of-interest–based analyses. Early and delayed post-ferumoxytol imaging will be compared to assess time-dependent USPIO redistribution across vascular and extravascular compartments. In patients undergoing surgical resection, imaging-derived measures of USPIO uptake will be correlated with tissue-based markers of inflammation and microvascular proliferation. Spatially resolved elemental iron maps derived from LA-ICP-MS will be compared with adjacent histological sections to support spatial validation of imaging-defined USPIO uptake and compared with corresponding MRI-derived USPIO-sensitive metrics.

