### Statistical analysis

2.9.

Differences between ROI volumes on post-GBCA T_1_-weighted and delayed (24–48 hour) USPIO-enhanced T_1_-weighted images will be evaluated using overlap measures, the Dice similarity coefficient (DSC) and Jaccard similarity coefficients (JSC), and the Structural Similarity Index Measure (SSIM) [43,44].

To satisfy primary endpoints, the associations between imaging-derived and tissue-derived parameters will be assessed using Pearson’s product-moment correlation coefficient for approximately normally distributed variables, or Spearman’s rank correlation coefficient for non-parametric or non-linear associations. Secondary analyses will assess temporal changes in imaging metrics, spatial overlap between GBCA and delayed ferumoxytol signal, and associations between USPIO-sensitive metrics and DCE-MRI, ASL and DTI-derived parameters. Comparisons between tumor subgroups, including glioma subtype and VS growth status, will be performed using t-tests or ANOVA where assumptions are met, or suitable non-parametric alternatives where appropriate [14]. These subgroup analyses will be exploratory and interpreted as hypothesis-generating.

Temporal changes in voxel-wise and whole tumor ROI imaging metrics (T_2_, T_2_*, R_1_, QSM-derived susceptibility values) within each tumor voxel will be evaluated using a repeated-measures ANOVA with Greenhouse–Geisser correction for non-sphericity and repeated-measures mixed-effect modeling [45]. Mixed-effects modeling will be preferred where repeated-measures datasets are incomplete. To address multiplicity, analyses will be pre-specified by endpoint hierarchy. For ROI-based secondary analyses involving multiple imaging metrics, false discovery rate correction or Holm–Bonferroni correction will be applied as appropriate. Voxel-wise analyses will be treated as exploratory and will use spatially appropriate correction methods, such as cluster-level correction or false discovery rate correction, where feasible. Findings from these exploratory analyses will be interpreted as hypothesis-generating, rather than confirmatory.

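### The analysis lists use T2 and T2* times and omit the R2 and R2* rates that the study's own hypothesis names, so the size of a T2* change depends on baseline T2* as well as on uptake

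*Protocol article*

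**What the plan says.** All references are to the protocol article.

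- **2.9 Statistical analysis** gives the variables for change over time as "Temporal changes in voxel-wise and whole tumor ROI imaging metrics (T_2_, T_2_*, R_1_, QSM-derived susceptibility values". The models are additive: the changes "will be evaluated using a repeated-measures ANOVA with Greenhouse–Geisser correction for non-sphericity and repeated-measures mixed-effect modeling".
- **2.8 Data collection, management, and analysis** lists "ferumoxytol-sensitive imaging markers (T_2_, T_2_*, SWI and SELFI values, QSM derived susceptibility values" as the markers to be related to perfusion, permeability and diffusion measures.
- **2.5.1 Post-scan processing** states "SELFI values will be compared with maps of quantitative relaxometry values (T_2_*, T_2".
- **1.2 Objectives**, hypothesis 4, uses the rate: "susceptibility based measures of delayed USPIO uptake (e.g., QSM, R2* mapping) will be greater in growing VS, relative to non-growing tumors". Hypothesis 3 speaks more loosely of T2*-based measures.
- **2.3.1 Imaging protocol** (text after Figure 2) names both forms without choosing: "delayed ferumoxytol assessment will prioritize T_2_, T_2_*/R_2_/R_2_*/SWI and QSM-derived measures". It also confirms that the rates will be available: "The acquisition of R_1_, R_2_, R_2_*, T_2_*, T_2_, SWI and QSM data across pre-contrast, post-GBCA, early post-ferumoxytol and delayed post-ferumoxytol timepoints".

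The article does not say how voxel values are summarized over a region of interest (ROI). It gives no T2* or R2* values.

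**The concern.** The lists in 2.5.1, 2.8 and 2.9 are not consistent with 1.2 and 2.3.1. The rate named in hypothesis 4 is missing from the lists that say what is analysed. The transverse measures are also treated differently from the longitudinal one, which 2.9 enters as R1. Hypothesis 4 predicts a measure that is greater in growing tumors; R2* rises with uptake, whereas T2* falls.

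The scale matters because ferumoxytol adds a term to the relaxation rate. The change in rate does not depend on where the tumor started. The change in time does: the same added rate shortens a long T2* by more milliseconds than a short one. Three uses are exposed:

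1. comparisons of T2* change between tumors, such as glioma against vestibular schwannoma (VS) or growing against static VS, if baseline T2* differs between them;
2. correlation of T2* change with macrophage density across patients;
3. the question of which quantitative measure is best (hypothesis 3 and the first secondary endpoint), where T2* could look worse than QSM because of its scale and not its biology.

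A second issue depends on how regions are summarized. An arithmetic mean of voxel T2* gives most weight to voxels without uptake. That matters if uptake is focal, and section 1.1.1 describes macrophages in VS as concentrated in Antoni B areas.

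**Working it through.** The plan states no figure that could be reproduced, and its sample size of 39 rests on feasibility. All T2*, R2* and focal-fraction values below are assumptions.

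**Baseline dependence.** Let T be baseline T2* in ms, and let uptake add d per second to R2*. Then T2* after uptake = 1000 / (1000/T + d).

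| Baseline T2* | After +10 /s | Change in T2* | Relative change | Change in R2* |
|---|---|---|---|---|
| 40 ms | 1000/(25 + 10) = 28.6 ms | -11.4 ms | -28.6% | +10 /s |
| 60 ms | 1000/(16.7 + 10) = 37.5 ms | -22.5 ms | -37.5% | +10 /s |
| 80 ms | 1000/(12.5 + 10) = 44.4 ms | -35.6 ms | -44.4% | +10 /s |

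The spread is about threefold (35.6/11.4 = 3.1) with identical uptake. Percentage change narrows it but does not remove it.

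The order of two tumors can also reverse. With baseline 40 ms and +20 /s, T2* falls to 1000/45 = 22.2 ms, a change of -17.8 ms. With baseline 60 ms and +10 /s the change is -22.5 ms. The tumor with twice the uptake shows the smaller fall.

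**Effect on correlation.** A noise-free simulation (4,000 runs, n = 15) drew uptake as log-normal with median 15 /s and log SD 0.5, and baseline T2* as log-normal around 50 ms. The table gives the mean correlation of true uptake with the fall in T2*.

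| Log SD of baseline T2* | Pearson | Spearman |
|---|---|---|
| 0.1 | 0.83 | 0.83 |
| 0.2 | 0.62 | 0.62 |
| 0.3 | 0.45 | 0.47 |
| 0.4 | 0.35 | 0.37 |

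With the change in R2* the correlation is 1 by construction. Ranks do not help, because baseline changes the order of the tumors and not only the shape of the relation.

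**Focal uptake, only if the ROI summary is an arithmetic mean of T2*.** Assume baseline 50 ms (20 /s), with 20% of voxels affected. Mean T2* = 0.8 × 50 + 0.2 × 1000/(20 + d). Converting this mean back to a rate and subtracting 20 gives the apparent rise, to compare with the true mean rise of 0.2 × d.

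| d in the focus | Mean T2* | Apparent rise | True mean rise | Share recovered |
|---|---|---|---|---|
| +10 /s | 46.7 ms | 1.43 /s | 2 /s | 71% |
| +20 /s | 45.0 ms | 2.22 /s | 4 /s | 56% |
| +50 /s | 42.9 ms | 3.33 /s | 10 /s | 33% |
| +100 /s | 41.7 ms | 4.00 /s | 20 /s | 20% |

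Inverting each voxel before averaging recovers the true mean rise exactly.

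**The case against.** The strongest reply is that the article has not chosen times over rates. Section 2.3.1 names R2 and R2* for delayed assessment, hypothesis 4 names R2*, and a condensed article may leave derived variables to a fuller document. This stands in part: rates have not been abandoned, and a reader who inferred that they had would be wrong. But 2.9 does state its variables, and that list does not match 1.2 and 2.3.1.

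Second, change over time is assessed within each tumor, and a rise in R2* lowers T2* at any baseline. This stands. The direction of within-tumor change is safe; the problem concerns its size when tumors are compared or correlated. The article does not name T2* change as the variable for subgroup comparisons, so the exposure there is possible, not certain.

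Third, other measures are planned. The same sentence in 2.9 includes QSM susceptibility, which is close to linear in concentration. SELFI uses log signal ratios, which are proportional to the change in R2* if decay is mono-exponential, although 2.5.1 calls SELFI investigational and not stand-alone. Voxel-wise analysis avoids averaging but keeps the baseline dependence if done in T2*. The option of Spearman's coefficient answers curvature, not baseline.

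A reader might also infer that focal uptake is largely lost. The documents do not support that. No ROI mean is specified, and even with one, weak focal uptake is mostly retained (71% at +10 /s).

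Finally, the temporal analysis is secondary, voxel-wise and subgroup results are labeled exploratory, and the primary endpoint is worded in terms of susceptibility changes. This limits the weight of the point but does not remove it.

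**Conclusion.** The point holds as an inconsistency with a real analytic consequence. Sections 2.8 and 2.9, and the relaxometry comparison in 2.5.1, list T2 and T2* and omit R2 and R2*, which the study's own hypothesis and imaging section name. That contrast adds to the rate, so that absolute T2 or T2* change depends on baseline, is arithmetic and needs no assumption about this study. Its size does: about threefold over assumed baselines of 40 to 80 ms at +10 /s. How far it distorts between-tumor comparisons, correlation with macrophage density or the ranking against QSM depends on how much baseline T2* varies, which the article does not give.

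The dilution of focal uptake is conditional on an arithmetic T2* mean and matters mainly for intense foci. The point does not show that the primary endpoint fails or that the temporal tests mislead on direction. It is worth correcting because the pilot is meant to yield preliminary effect sizes for later studies, and T2* effect sizes would carry the baseline dependence with them.

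**What to change.** In 2.8 and 2.9, name the change from the pre-contrast scan in R2 and R2* as the analysed relaxometry variables, in line with hypothesis 4, section 2.3.1 and the existing use of R1. State that maps are inverted voxel by voxel before any ROI summary, and name that summary. T2 and T2* maps can stay as descriptive output, including in the SELFI comparison in 2.5.1.

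The cost is wording and a voxel-wise inversion of maps already planned; no new scans are needed. One small downside is that R2* is noisy in voxels with very short T2*, which a fit-quality mask or an ROI median can handle.

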### Monitoring

2.10.

Recent large, multicenter registry studies indicate that when given as a slow infusion, USPIO has a favorable side-effect profile compared to the more commonly used GBCA compounds [21], with adverse reactions occurring in <2% of administrations [19]. Any adverse events thought to be related to the ferumoxytol infusion will be recorded within the case report form for each participant. Any symptoms recognized as potential side effects of parenteral iron infusion (acute myalgia, arthralgia, headache, chest pressure, and/or back pain) will be documented along with the duration of symptoms, time of onset post start of infusion and any treatment required.

Definition of serious adverse events (SAE) will be in line with NHS REC/HRA guidance on non-CTIMPs [46]. Wheezing, stridor, periorbital edema, or persistent hypotension occurrence following ferumoxytol infusion are thought to be very rare. Any such reactions to ferumoxytol (severe enough to warrant treatment with intravenous fluids and/or methylprednisolone) will therefore be classed as an SAE.

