**Figure 2. f0002:**
[figure not shown]
Study design and scanning workflow.

On the first visit, patients undergo a baseline advanced MRI protocol at 3T, including: structural T_1_W and T_2_ FLAIR imaging (glioma only), baseline T_1_ relaxivity (R_1_) mapping (measured using a variable flip angle acquisition), SWI, T_2_ and T_2_* mapping, QSM, and DTI. Amide proton transfer (APT) imaging, a chemical exchange saturation transfer MRI technique that is sensitive to changes in proteins and peptides containing amide groups in tissue, is also performed for recruited glioma patients. It is not performed for participants with VS, as its application in the inferior brain and skull base is often limited by artifacts arising from B_0_ field inhomogeneities at air–tissue interfaces, particularly near the paranasal sinuses and external auditory canals [31]. For measuring tumor perfusion and tumor microvascular characteristics (including endothelial permeability) a multi-delay ASL acquisition and a dual-injection, dual–temporal resolution DCE-MRI acquisition is also collected. During the DCE-MRI protocol, administration of a GBCA (gadoterate meglumine; Dotarem®, Guerbet S.A.; dose of 0.2 mmol/kg) is performed, and is followed by post-contrast T1W imaging and repetition of the pre-contrast T_1_, T_2_ and T_2_* mapping, SWI, and QSM protocols. An overview of included sequences and acquisition parameters are provided in Supplementary Table S1.

After the initial baseline MRI scan, patients receive ferumoxytol at a dose of 5 mg/kg (up to maximum dose of 510 mg) as a slow intravenous infusion over 30 minutes. Patient observations (blood pressure, heart rate, temperature) are performed regularly during the infusion and up to 30 minutes afterward, due to a small risk of serious hypersensitivity reactions following IV iron infusions.

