### Sample size and tumor groups

2.7.

The planned number of participants is 39 (12 sporadic VS, 12 NF2-VS patients, 15 glioma patients). This sample size reflects feasibility and the expected recruitment capacity of a single-center pilot study requiring serial advanced MRI over three days, ferumoxytol infusion, and, in surgical participants, tissue acquisition for imaging-histology comparison. Although glioma and VS are biologically distinct, both are characterized by macrophage-rich inflammatory tumor microenvironments that are implicated in tumor growth, progression and treatment response. The inclusion of both intra-axial gliomas and extra-axial VS permits assessment of our hypotheses across two clinically important CNS tumor settings with differing characteristics.

This pilot study will allow the evaluation of recruitment feasibility, scan completion rates, tolerability, missing data rates, USPIO-sensitive MRI metrics, and preliminary effect sizes for imaging-histology associations. Subgroup analyses by tumor type, VS growth status and glioma transformation status will therefore be interpreted as exploratory, to inform future larger-scale studies.

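### Outside the listed infusion symptoms and SAEs, adverse events reach the case report form only if attributed to ferumoxytol, so a tolerability rate for the whole two-agent procedure would be incomplete

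*Protocol article*

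**What the plan says.** Section 2.10 (Monitoring) of the protocol article gives three ways for an event to be recorded.

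1. A general rule based on judged cause: "Any adverse events thought to be related to the ferumoxytol infusion will be recorded within the case report form for each participant".
2. A rule based on symptom type: "Any symptoms recognized as potential side effects of parenteral iron infusion (acute myalgia, arthralgia, headache, chest pressure, and/or back pain) will be documented", together with the "duration of symptoms, time of onset post start of infusion and any treatment required". No causal judgement is attached to it.
3. A rule for serious events: "Definition of serious adverse events (SAE) will be in line with NHS REC/HRA guidance on non-CTIMPs". Certain hypersensitivity signs are added: "Any such reactions to ferumoxytol (severe enough to warrant treatment with intravenous fluids and/or methylprednisolone) will therefore be classed as an SAE".

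Section 2.7 (Sample size and tumor groups) says the pilot will allow "evaluation of recruitment feasibility, scan completion rates, tolerability, missing data rates" to be assessed. Tolerability is not among the primary or secondary endpoints in section 1.2.

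Section 2.3.1 (Imaging protocol) sets the order of the two agents. During the baseline perfusion scan, "administration of a GBCA (gadoterate meglumine; Dotarem®, Guerbet S.A.; dose of 0.2 mmol/kg) is performed". Ferumoxytol is infused over 30 minutes after that scan, at the same visit. Blood pressure, heart rate and temperature are observed during the infusion and for up to 30 minutes after it. Patients return for scans at 24 and 48 hours.

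**The concern.** The general rule makes a causal judgement the condition for recording an event, when that judgement should be one of the things recorded. Each participant receives gadolinium and then ferumoxytol at one visit, with no control group, so for events that begin after the infusion starts the separation of the two agents rests on clinical opinion. Section 2.3.1 considers the interaction of the agents for image interpretation only.

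At stake is what a later study could learn about tolerability. It would presumably adopt the whole procedure, gadolinium scan included. If non-serious events attributed to gadolinium, to the scanning or to the tumor are left off the form, the any-cause rate for that procedure can be too low but not too high. The rate for ferumoxytol alone would inherit whatever errors the attribution contains, in either direction. Neither could be repaired afterwards, because an event that was not written down cannot be reclassified.

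**Working it through.** **Step 1. Which events have a stated route.** Setting the three rules of section 2.10 side by side:

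| Event | Stated route |
|---|---|
| Any event attributed to ferumoxytol | Yes, general rule |
| One of the five listed symptoms, whatever its cause | Yes, by symptom type |
| Serious adverse event | Yes, by external guidance (not shown; taken here to apply whatever the cause) |
| Non-serious, not listed, attributed to gadolinium | None |
| Non-serious, not listed, judged unrelated | None |

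For example, mild wheezing attributed to gadolinium falls in the fourth row. It is not one of the five symptoms, and the added SAE rule covers reactions to ferumoxytol that need treatment. Even for listed symptoms, onset is timed from the start of the infusion; no time relative to the gadolinium injection is mentioned.

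**Step 2. The denominator.** Section 2.7 gives 12 + 12 + 15 = 39, which agrees with its stated total. The number is justified by feasibility, so there is no power calculation to reproduce.

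**Step 3. What one participant is worth.** 1/39 = 2.6 percentage points. Section 2.10 cites adverse reactions in under 2% of administrations. At exactly 2%:

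- expected number of reactions: 39 × 0.02 = 0.78
- chance of at least one: 1 − 0.98^39 = 54.5%

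Exact (Clopper-Pearson) two-sided 95% limits:

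| Participants with an event | Rate | 95% limits |
|---|---|---|
| 0 of 39 | 0% | 0% to 9.0% |
| 1 of 39 | 2.6% | 0.1% to 13.5% |
| 2 of 39 | 5.1% | 0.6% to 17.3% |

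A single attribution decision can therefore put the observed rate below or above the cited figure.

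**Step 4. Illustration of a shortfall (assumed inputs).** The document gives neither the any-cause rate of events outside the three routes nor the share that would be attributed to ferumoxytol. For non-serious events outside the five symptoms, participants recorded = 39 × rate × share attributed to ferumoxytol:

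| Assumed any-cause rate | Participants with an event | Recorded if 25% attributed | Recorded if 75% attributed |
|---|---|---|---|
| 5% | 1.95 | 0.49 | 1.46 |
| 10% | 3.9 | 0.98 | 2.93 |
| 20% | 7.8 | 1.95 | 5.85 |

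The proportional loss is simply one minus the assumed share, so the table shows scale and proves nothing about this study.

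**The case against.** The strongest reply is that the general rule should not be read alone. The sentence after it documents the commonest infusion symptoms by type, with onset, duration and treatment, so a headache blamed on the tumor is still written down. SAEs have their own route, and vital signs are observed in every participant. This stands. A reader might infer from the general rule that only ferumoxytol-related events are recorded, or that unattributed events are never written down; section 2.10 does not support either statement.

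Second, saying that related events will be recorded does not say that others will not be, and the full protocol and case report form are not shown. This stands in part. The form may well collect more. But the article states a criterion for entry, which is a choice made and not a detail left out; if the form is wider, the sentence misdescribes it and should be corrected.

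Third, the agents are separated in time: several acquisitions follow the gadolinium injection before the infusion begins. An event before the infusion is thus not ambiguous. That weakens any claim that attribution is mere guesswork, but it does not help recording, since an event clearly due to gadolinium is one for which no route is stated unless it is listed or serious.

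Fourth, tolerability is one word in a feasibility list, and with 39 participants sampling error exceeds any plausible filtering effect. The first part stands and limits the importance of the point. The second is true of precision, but a wide interval does not excuse an avoidable, one-directional loss of events.

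**Conclusion.** The point holds in a limited form. As written, section 2.10 states no route for non-serious events that fall outside the five listed symptoms and are attributed to gadolinium or judged unrelated, while section 2.7 promises an evaluation of tolerability. A rate for the whole procedure built on these records would be incomplete and could not be re-attributed later. One participant counted or not is worth 2.6 percentage points, against a cited rate of under 2%.

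The size of the loss is unknown; the illustration rests on assumed rates. A reader might also infer that a safety signal from giving both agents at one visit would be missed. The document does not support that: such a reaction would be expected once ferumoxytol had started, when attribution to it, and so recording, is most likely, and serious reactions have their own route.

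The conclusion assumes that the case report form follows the published rule and that SAEs are recorded whatever their cause. It concerns a descriptive feasibility measure. The primary imaging-histology analysis and the listed secondary endpoints are untouched.

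**What to change.** Change the general rule in section 2.10 so that recording no longer depends on attribution:

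- Record every adverse event from the first gadolinium injection to the 48-hour scan.
- For each, enter the onset time relative to the gadolinium injection and to the start of the ferumoxytol infusion.
- Enter relatedness in separate fields: to gadolinium, to ferumoxytol, or indeterminate.
- Ask about events at the 24- and 48-hour visits, which already take place.
- Report the number and proportion of participants with any event first, then by attribution, with exact confidence intervals. The column for events attributed to ferumoxytol is the one to set beside the cited rate of under 2%, which is itself a rate of reactions.

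If the case report form already collects all events, correcting the sentence in section 2.10 is enough.

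The cost is a form change, a few minutes at visits already planned, and a longer list of minor events. For participants already scanned under the present rule, report separately from those recorded under the new one, since the missing events cannot be recovered.
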